## Methods

### Design

The effectiveness of OVK will be studied by means of a randomized controlled trial with two conditions: intervention versus control (no intervention) (see Figure 1). We have chosen not to include a third condition with an alternative program, because there is no existing Dutch school-based universal depression prevention program for young adolescents, and because of financial constraints. Therefore, the control condition correctly reflects "care as usual". Randomization of schools, stratified by educational level, to either one of the conditions will be conducted by an independent statistician of the Radboud University. Stratifying by educational level is needed to evenly distribute educational level across intervention and control group, despite the small number of schools. Randomizing between schools (as opposed to within schools) will have the following benefits: It will minimizes contamination; adolescents in the control condition are not influenced by their friends in the experimental arm, and it will provide all adolescents in the second grade of a particular school with the opportunity to participate in the prevention program.

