**Figure 1 F1:**
[figure not shown]
**Study design**.

To test the (long term) effectiveness of the program, the outcomes will be assessed through self-report questionnaires approximately 1 month before the start of the program (baseline: T1), directly after the program (T2), and 6 (T3), 12 (T4), 18 (T5) and 24 (T6) months after the end of the program. Adolescents in the control condition will complete the questionnaires at exactly the same time points. Parental self-reports will be administered at baseline only. Adolescents assigned to the experimental condition will receive the OVK program, and adolescents in the control condition will receive care as usual (no program). As a reward for participation in the study, the schools in the control condition will receive a training for teachers in the OVK program between T3 and T4, on the strict condition that they will not provide the program to the adolescents who participated in the study.

OVK will be incorporated into the school curriculum; the 16-lesson program will be delivered once a week by trained psychologists to groups with a maximum of 15 adolescents. Incorporating the program in the school curriculum enables us to truly provide the program to all adolescents in a certain grade. As a result, high attendance rates will be assured and no stigmatization will occur. To keep the attrition rates at a minimum, all adolescents absent at a given measurement will be provided another possibility in the same time period to complete the questionnaire. Also, adolescents who leave school will be asked, with assistance of the school, to continue participating in the study. The trial is registered at the Dutch Trial Register: NTR2879.

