### Measures

The primary outcome will be the level of depressive symptoms at 6, 12, 18 and 24 months follow up measured with the Child Depression Inventory (CDI) [42], which is reliable and valid [43,44]. Possible mediators will be coping, cognitive bias, self-efficacy, hopelessness and optimism. The Children's Coping Strategies Checklist Revision 1 [45] will be used to assess coping styles. Cognitive bias will be measured with a questionnaire specifically developed to assess the cognitive biases addressed in OVK [46]. Self-efficacy will be assessed with the Self-Efficacy Questionnaire for Children SEQ-C [47], which has satisfactory internal consistency and good validity. Hopelessness will be measured with Beck's Hopelessness Scale (BHS) which has good reliability and validity [48]. Optimism will be measured with LOT-R which has good validity and reliability properties [49].

The 'negative' secondary outcomes will be the level of anxiety, truancy and substance use. Anxiety will be assessed with the Revised Children's Manifest Anxiety Scale (RCMAS) [50]. The RCMAS is a widely used questionnaire that assesses anxiety symptoms in children and adolescents. This scale has demonstrated good reliability and correlates with other measures of anxiety symptoms. Truancy will be measured through a self-report question: 'How many hours did you skip school the past 4 weeks?'. Widely used standard instruments will be administered to tap the frequency and intensity of alcohol [51,52] and tobacco use [53,54]. Positive secondary outcomes are life satisfaction, happiness, school grades and attitude, and participation in friendship groups. Life satisfaction will be measured with the Students Life Satisfaction Scale [55]. The SLSS assessed adolescents' global satisfaction or contentment. Studies have found the SLSS to have good internal consistency and test-retest reliability and to correlate highly with other subjective well-being measures [55]. Happiness will be measured with the Cantril Ladder [56]. Academic performance will be assessed by asking adolescents to list their last grades on core subjects. Clique membership and friendships will be measured with one sociometric item: "Who are your best friends?". Information on socio-demographic factors, for example, age, sex, ethnicity, religious affiliation, and educational level, will also be obtained.

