### Data analysis

Data will be analyzed in accordance with the intent-to-treat principle and for the completers only. Multiple imputations will be used for missing observations at follow-ups. The hypotheses will be tested with regression analyses for dichotomous outcome measures in MPLUS 5.1 [65,66]. Additional analyses will be conducted to test effects of the intervention on development of depressive symptoms using latent growth curve (LGC) modeling [66], in which the intercept and slope of levels of depressive symptoms using scale scores (as we will have 6 assessments) are modelled, and effects of condition can be examined. We will check for possible baseline differences between the two conditions in demographic variables (e.g. age, gender, school level, and ethnic background) and depressive symptoms. Moreover, variables that show different distributions between the two groups will be entered as confounders in all models testing the effectiveness of the program. The cluster effect-students were 'nested' in classes-will be handled by getting robust variance related estimates based on the first order Taylor series linearization method using Stata's procedures for design based analyses [65]. Reporting of the results of the study will be in accordance with the CONSORT statement [67].

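### Mediators and secondary outcomes have no prespecified adjustment for their own T1 score: the baseline check names only demographics and depressive symptoms, and adjustment follows observed imbalance

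*Protocol article*

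**What the plan says.** The Data analysis section sets a covariate rule in two steps. The check comes first: "We will check for possible baseline differences between the two conditions in demographic variables (e.g. age, gender, school level, and ethnic background) and depressive symptoms". The consequence follows: "variables that show different distributions between the two groups will be entered as confounders in all models testing the effectiveness of the program". No mediator or secondary outcome is named in the check.

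The variables concerned are listed under Measures: "Possible mediators will be coping, cognitive bias, self-efficacy, hopelessness and optimism"; "The 'negative' secondary outcomes will be the level of anxiety, truancy and substance use"; "Positive secondary outcomes are life satisfaction, happiness, school grades and attitude, and participation in friendship groups". On grades it adds: "Academic performance will be assessed by asking adolescents to list their last grades on core subjects".

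Baseline values are planned. In the Design section, below Figure 1, the article says "the outcomes will be assessed through self-report questionnaires approximately 1 month before the start of the program (baseline: T1"). The only model described as using an outcome's own T1 value is the latent growth curve over the six assessments, and it covers depressive symptoms alone.

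Randomisation is by school, stratified by educational level, and the Design section justifies the stratification with the words "despite the small number of schools".

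**The concern.** Goals 2 and 3 of the article (mediating mechanisms and secondary outcomes) rest on comparing arms on variables other than depressive symptoms. For each of these, its own T1 score is likely to be among the most useful covariates, and it is already being measured. Under the stated rule, a model for anxiety or grades could carry age, ethnic background and the baseline depression score, but not T1 anxiety or T1 grades.

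The rule can be read in two ways, and neither prespecifies the adjustment:

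- **Narrow reading.** The variables that may be entered are those just checked. Own-T1 scores of mediators and secondary outcomes are then not provided for.
- **Broad reading.** Any variable that differs may be entered. Own-T1 scores then enter only if an imbalance is seen, so the covariate set depends on the data and may differ from outcome to outcome.

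With few randomised schools, arms can differ at T1 on grades, truancy or smoking for reasons unrelated to the programme. At stake are the interpretation of individual secondary results and the precision that the T1 wave would give.

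**Working it through.** The article gives no figure for baseline adjustment, so there is none to reproduce.

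**Inputs from the article:** planning effect 0.20; 662 pupils per condition; at most 20% attrition. Analysed pupils per arm: 662 × 0.8 = 529.6, about 530 (about 1,060 in total).

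**Inputs assumed, because the article gives none:** 8 to 12 schools, so k = 4 to 6 per arm; school ICC 0.02 to 0.10; T1-to-follow-up correlation 0.6 between pupils within a school and 0.8 between school means.

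**Step 1. SD of the chance T1 difference between arms, in outcome SD units:**

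SD = √[2 × (ICC/k + (1 − ICC)/530)]

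Lowest case (ICC 0.02, k = 6): √[2 × (0.00333 + 0.00185)] = 0.102. Highest case (ICC 0.10, k = 4): √[2 × (0.02500 + 0.00170)] = 0.231.

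**Step 2. Share of a T1 difference expected in the unadjusted follow-up contrast:**

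[0.8 × ICC/k + 0.6 × (1 − ICC)/530] ÷ [ICC/k + (1 − ICC)/530]

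**Step 3. Variance left after subtracting 0.6 × the T1 contrast:** the pupil part is multiplied by 1 + 0.36 − 2 × 0.6 × 0.6 = 0.64, and the school part by 1 + 0.36 − 2 × 0.6 × 0.8 = 0.40. The ratio to the unadjusted variance is

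[0.40 × ICC/k + 0.64 × (1 − ICC)/530] ÷ [ICC/k + (1 − ICC)/530]

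| ICC | k per arm | SD of T1 difference | Share carried over | Variance cut |
|---|---|---|---|---|
| 0.02 | 6 | 0.102 | 73% | 51% |
| 0.02 | 4 | 0.117 | 75% | 54% |
| 0.05 | 6 | 0.142 | 76% | 56% |
| 0.05 | 4 | 0.169 | 77% | 57% |
| 0.10 | 6 | 0.192 | 78% | 58% |
| 0.10 | 4 | 0.231 | 79% | 58% |

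A simulation of school means (4,000 replicates) gave SDs of 0.102 to 0.230 and variance cuts of 51 to 59%, in agreement. A T1 difference of one SD therefore shifts the unadjusted contrast by about 0.102 × 0.73 = 0.07 to 0.231 × 0.79 = 0.18.

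**Step 4. A lower bound from the plan's own sample size.** An effect of 0.20 with two-sided alpha 0.05 and power 0.80 needs 393 per arm. The factor left for clustering and imputation together is 529.6/393 = 1.35. If all of it were clustering, the SD would be √(2 × 1.35/530) = 0.071. With no clustering it would be √(2/530) = 0.061, and the variance cut would be 1 − 0.64 = 36%.

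**Step 5. Behaviour under no effect.** A second simulation ran 2,000 trials per setting, with 3 or 5 schools per arm, school ICC 0.01 to 0.05, class ICC 0.01, the same correlations and class-robust standard errors:

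| Quantity | Unadjusted | Own-T1 adjusted |
|---|---|---|
| Mean shift towards the imbalance, trials with T1 difference above 0.1 SD | 0.11–0.19 | 0.02–0.05 |
| Rejection in those trials | 36–59% | 14–41% |
| Rejection over all trials | 15–45% | 13–39% |

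T1 differences above 0.1 SD arose in 27 to 59% of trials. At school ICC 0, overall rejection was 5 to 6% with or without adjustment.

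**The case against.** A reader might infer that these T1 scores are never adjusted for, even when plainly unequal, and that chance school differences will be reported as programme effects. The article does not support this. Its confounder sentence speaks of variables without tying them to the preceding list, and nothing excludes mediator or secondary-outcome scores. The unadjusted contrast is unbiased over the randomisation. Nor would a baseline difference pass through almost whole: under the assumed correlations about 73 to 79% does.

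It can also be said that a condensed article may leave the covariates of secondary models to a fuller plan. That would be decisive if the article were silent. It is not: it states a rule for all effectiveness models, and that rule makes adjustment depend on observed imbalance.

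Four limits on the size stand:

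- School count, ICC and correlations are assumed. One pair of correlations cannot fit anxiety, grades, smoking and a single truancy item equally well. The article's own sample size leaves room for only a small clustering allowance, although its ICC is not given and need not apply to grades or smoking.
- Stratification by educational level removes some imbalance, probably most for grades, and the calculations ignore it.
- The variance cut is for a linear contrast. The article's named hypothesis tests are regressions for dichotomous outcomes. If these are logistic, adjustment changes the odds ratio being estimated and the 51 to 59% does not transfer.
- Most of the excess overall rejection in the simulation comes from clustering on classes while schools are randomised. That is a separate problem, which own-T1 adjustment does not cure.

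**Conclusion.** The point holds in a limited form. The stated rule does not name the T1 scores of mediators and secondary outcomes and, at best, lets them in after an imbalance has been observed. The consequences are bias conditional on the realised imbalance and lost precision.

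Under the assumed 8 to 12 schools, about 1,060 analysed pupils and school ICC of 0.02 to 0.10, the SD of the chance T1 difference is about 0.10 to 0.23, against a planning effect of 0.20. It would be only 0.06 to 0.07 if clustering is no larger than the sample size allows for. Own-T1 adjustment would cut the variance of a linear contrast by about 51 to 59% under the assumed correlations of 0.6 and 0.8. The change should be made: it concerns goals 2 and 3, the likely gain is material and the cost is slight.

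**What to change.** Add to the Data analysis section: *Every model for a mediator or secondary outcome includes that variable's own T1 score as a prespecified covariate, whatever the observed balance. For school grades, this is the T1 grade in the same subjects.*

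Where an outcome is dichotomised and modelled by logistic regression, state that the odds ratio is conditional on the T1 score.

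The cost is about one degree of freedom per model. No new data are needed, because the T1 wave already collects the outcomes.

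### Adjustment variables in the main regressions are chosen by observed baseline imbalance, so neither baseline CDI nor the educational-level stratum is assured a place

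*Protocol article*

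**What the plan says.** The Data analysis section announces a check for baseline differences in "demographic variables (e.g. age, gender, school level, and ethnic background) and depressive symptoms". It then gives the article's one statement on covariates: "Moreover, variables that show different distributions between the two groups will be entered as confounders in all models testing the effectiveness of the program". It gives no test or threshold for calling two distributions different, and it names no variable that enters whatever the balance.

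The same section describes two kinds of model. The main one is given as "The hypotheses will be tested with regression analyses for dichotomous outcome measures in MPLUS 5.1". The additional one is a latent growth curve model for CDI scale scores over all six assessments, T1 to T6.

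The Design section describes "Randomization of schools, stratified by educational level, to either one of the conditions" and gives the reason: "Stratifying by educational level is needed to evenly distribute educational level across intervention and control group, despite the small number of schools". Outcomes are first measured at T1, about a month before the program starts. The Measures section lists sex and educational level among the data collected.

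**The concern.** A covariate earns its place by how well it predicts the outcome, or because the randomisation was stratified on it. Observed imbalance measures neither. Three consequences follow.

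- **Stratum.** Schools are stratified on educational level so that it comes out even, yet it is assured entry only if it comes out uneven. The better the stratification works, the more likely the analysis is to ignore it.
- **Baseline CDI.** The first goal is to limit the increase in depressive symptoms, and T1 CDI can be expected to predict later CDI. In the main regressions it is assured entry only after a chance difference.
- **Data-driven model.** What is adjusted for in the effectiveness models is not known until the baseline data have been inspected. In a logistic model the odds ratio also changes meaning with the covariates, so chance imbalance decides which effect is reported.

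Power and prespecification are at stake, not the validity of the test.

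**Working it through.** **1. The plan's own sample size.** Inputs from Participants and procedure: effect size 0.20 (read here as a standardised mean difference), alpha .05 (taken as two-sided; the article does not say), power .80, 20% attrition, 662 per condition.

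- n per arm = 2 × (1.960 + 0.842)² / 0.20² = 393 after rounding up.
- With 20% attrition: 393 / 0.8 = 492 after rounding up.
- Remaining factor in 662: 662 × 0.8 / 393 = 1.35, for clustering and imputation loss together.

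The intraclass correlation, cluster size and imputation loss are not given, so 662 can be neither confirmed nor called wrong. The point does not depend on it. An effective 393 per arm is used below, which is what the planned 80% power implies.

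**2. Continuous CDI score, always adjusting for T1 CDI.** Adjustment multiplies the residual variance by 1 − r², where r is the baseline-to-follow-up correlation. The article gives no value, so r is an assumption. Power = Φ(0.20 × √(393/2) / √(1 − r²) − 1.96), where 0.20 × √(393/2) = 2.804.

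| Assumed r | 1 − r² | Power |
|---|---|---|
| none (unadjusted) | 1.00 | 0.80 |
| 0.4 | 0.84 | 0.86 |
| 0.5 | 0.75 | 0.90 |
| 0.6 | 0.64 | 0.94 |
| 0.7 | 0.51 | 0.975 |

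This is an individual-level approximation that keeps the factor of 1.35 unchanged by adjustment.

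**3. Dichotomised outcome, as in the main regressions.** Simulation with 1,500 runs per row and 393 per arm: a normal score shifted by 0.20, cut at an assumed 20% control prevalence, logistic regression, no clustering. The rule was represented by entering T1 CDI only when a t-test of baseline gave p < 0.05. That test is an assumption.

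| Assumed r | Never adjust | Always adjust | Rule | Gain from always adjusting | Mean OR, unadjusted → adjusted |
|---|---|---|---|---|---|
| 0.5 | 0.46 | 0.52 | 0.46 | 6 points | 0.70 → 0.66 |
| 0.6 | 0.49 | 0.57 | 0.49 | 8 points | 0.70 → 0.64 |
| 0.7 | 0.50 | 0.63 | 0.51 | 13 points | 0.69 → 0.59 |

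The never-adjust column should not vary with r; its spread is simulation noise (standard error √(0.25/1500) = 0.013). A separate simulation under the same assumptions gave 0.47/0.53/0.47, 0.51/0.59/0.51 and 0.50/0.60/0.50 for never/always/rule. The odds-ratio shift arises although the data-generating effect is the same: the adjusted ratio is conditional on T1 CDI and the unadjusted one is marginal.

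**4. Continuous score under the rule.** In 4,000 runs per setting, power for never/always/rule was 0.82/0.91/0.83 (r = 0.5), 0.80/0.93/0.81 (0.6) and 0.82/0.98/0.83 (0.7). T1 CDI entered in about 5% of runs, as a 5% test implies in unclustered data.

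**5. Type I error under the rule.** It was 0.036 to 0.044 for the continuous score and 0.034 to 0.055 for the dichotomised outcome (standard error √(0.05 × 0.95/1500) = 0.006). There is no sign of inflation.

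**The case against.** - **T1 CDI is not lost from every model.** This stands. The latent growth model uses all six assessments, so T1 CDI is in it whatever the balance, and that model speaks directly to the increase in symptoms. For it, only the stratum and the data-driven selection are at issue.
- **Power of 86–98% is not what the main regressions would gain.** This stands. A reader might take those figures as the size of the loss, but they belong to a continuous-score analysis. The dichotomised figures are the relevant ones for the stated main models, and both sets rest on an assumed r.
- **The article does not say that only flagged variables enter.** True: it says that flagged variables will enter, and a statistical analysis plan that is not shown may fix others. The finding is therefore not that a covariate list is missing. The stated rule itself selects by imbalance and assures entry on no other ground.
- **The stratum may still enter.** Also true. School level is among the variables checked, and with few schools its pupil-level distribution may differ despite stratification. It tends to be left out; it is not excluded.
- **With few schools, flags may be frequent.** A reader might infer that false flags will be common, for example 44–78% for at least one of five variables. Those figures need a 5% test that ignores clustering, five independent variables and design effects of 1.5 to 3, none of which the article gives. More frequent flags would also bring T1 CDI in more often and shrink the power loss, so both harms cannot be counted at full size. For one variable the flag probability of such a test is 2Φ(−1.96/√DE): about 9% at a design effect of 1.35 and about 26% at 3. T1 CDI would still stay out in roughly three trials of four at the upper end, and the model would be no less data-driven.
- **No invalid inference is shown.** This stands. A reader might infer an inflated false-positive rate, but the simulation, which ignores clustering, shows none.

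**Conclusion.** The point holds for the main hypothesis-testing regressions and, in part, for the latent growth model. Selection by imbalance leaves the adjustment set open until data are seen, tends to omit the randomisation stratum, and assures T1 CDI a place only by chance.

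For a dichotomised outcome the loss is roughly 6 to 13 percentage points of power for r between 0.5 and 0.7, given 20% prevalence, 393 effective pupils per arm and no clustering. The rule, read as a 5% test, recovers about one point of this at most. For the continuous score, power would rise from 80% to about 86–98% for r between 0.4 and 0.7. In logistic models the selection also decides which odds ratio is reported. Validity of the test is not in question, so this is a change that should be made rather than one on which the trial stands or falls.

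**What to change.** Replace the imbalance rule with a prespecified adjustment set:

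- **Main regressions:** always include the baseline CDI scale score (or the baseline value of the outcome analysed) and the educational-level stratum.
- **Latent growth model:** include the educational-level stratum as a fixed covariate. Keep T1 CDI as an indicator only; adding it as a covariate would enter it twice.
- **Baseline balance:** report it descriptively, without using it to choose covariates.
- **Other variables that look imbalanced:** adjust for them in a labelled sensitivity analysis.

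The cost is a few sentences in the Data analysis section. The plan already collects T1 outcomes and educational level, so no new data are needed.

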**Method:**

The effectiveness of OVK will be tested in a randomized controlled trial with two conditions, intervention (OVK) and control condition (care as usual). Schools are randomly assigned to research conditions. OVK will be incorporated in the school curriculum, maximizing program attendance. OVK consists of 16 lessons of 50 min, given by trained psychologists to groups of 11-15 students. OVK contains Cognitive Behavioral Therapy, social skills training, problem solving and decision making. Outcomes are measured at 6, 12, 18 and 24 months follow up, to monitor long term program effects. Primary outcome is level of depressive symptoms, secondary outcomes are: anxiety, hopelessness, cognitive bias, substance use, truancy, life satisfaction, coping, self-efficacy, optimism, happiness, friendship, school performance and school attitude. The questionnaires for students will be administered in the school setting. Parents will complete a questionnaire at baseline only.

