### Participants and procedure

Participants will be adolescents in their second year of secondary school (8th grade, ages 12-14) [28]. Secondary schools in the southern and middle part of the Netherlands will be approached to participate in the study. Only adolescents in middle school grade 8 will be included. We will ensure inclusion of low SES and ethnic minority groups, as well as different educational levels (Dutch middle school prepares adolescents for vocational up to university level). The exclusion criterion consists of parental refusal of their child's participation in the study. When schools show interest, they will be asked to participate with as many as possible second grade classrooms. We expect that-once included in the study-across the entire study period, approximately 80% of adolescents will provide complete data [33,34].

A meta-analysis on 17 controlled studies on PRP indicated the significant average effect size to be 0.20 at 12-months follow-up with the CDI > 13 score as cut-off [28]. Power analysis (G-power) based on this 12-month mean effect size takes into account a maximum of 20% attrition over time, as well as clustering of data in schools and loss of power due to multiple imputation. Based on this power analysis, sample sizes need to be 662 adolescents per condition (alpha < .05, power = .80); at least 1,324 adolescents will be included.

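### The fixed first-order linearised variance does not suit a trial that randomises a small number of schools; naming school as the cluster would not by itself make the arm test reliable

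*Protocol article*

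**What the plan says.** The unit of allocation is the school. The abstract says "Schools are randomly assigned to research conditions", and the Design section specifies "Randomization of schools, stratified by educational level, to either one of the conditions". The same section justifies stratification by the need to "evenly distribute educational level across intervention and control group, despite the small number of schools". No count of schools is given.

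Participants and procedure states that the power analysis allowed for attrition "as well as clustering of data in schools and loss of power due to multiple imputation".

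Data analysis then fixes the treatment of clustering: "The cluster effect-students were 'nested' in classes-will be handled by" obtaining "robust variance related estimates based on the first order Taylor series linearization method", through Stata's design-based routines. It names no degrees of freedom or reference distribution. It also says "The hypotheses will be tested with regression analyses for dichotomous outcome measures in MPLUS 5.1". Covariates enter only if a baseline check shows that they differ between conditions. School level is among the variables checked, but the stratification factor is not fixed as a covariate.

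**The concern.** First-order Taylor linearisation is justified as the number of independent clusters grows, and the number of pupils does not replace it. With few clusters the estimated variance is on average too small and itself imprecise, more so when clusters differ in size. Unequal sizes are likely here, because schools are asked to bring as many second-year classes as they can.

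The Design section recognises that schools are few and responds with stratification. The analysis section does not carry this through. As written it clusters on classes, which is a separate problem of level. The obvious repair is to substitute school for class and keep the rest of the sentence. That repair is needed, but it leaves a large-sample variance resting on few clusters. At stake are the error rate and the interval width of the programme comparison.

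**Working it through.** **Inputs from the article.** 1,324 pupils, 662 per condition, alpha 0.05, at most 20% attrition (Participants and procedure); schools randomised within educational level (Design); 10 leaders with 5-9 groups each and two groups per class (Program delivery).

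**Assumptions, not in the article.** Number of schools H, intraclass correlation (ICC), variation in school size, and the share of between-school variance that educational level explains.

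**The plan's own figure.** An effect size of 0.20 with 80% power needs 393 per arm (two-sided), and 393/0.8 gives 492 after attrition. Reaching 662 takes a further factor of 662/492 = 1.35 for clustering and imputation. The article does not break this factor down, so 662 can be neither reproduced nor faulted. The point does not depend on it.

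**Clusters as written.** 10 x 5 to 10 x 9 = 50-90 groups, so 25-45 intervention classes, and about 50-90 classes in total if the arms are equal. That number is adequate for linearisation, but a class is not the randomised unit.

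**School as cluster, equal sizes, no stratum effect (exact).** With factor H/(H-1), the linearised variance has expectation (H-2)/(H-1) of the unbiased one. The true rejection rate for critical value c is therefore P(|t with H-2 df| > c x sqrt((H-2)/(H-1))).

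- H = 8: sqrt(6/7) = 0.926. Normal: 1.96 x 0.926 = 1.815 on 6 df, 12.0%. t on 7 df: 2.365 x 0.926 = 2.189, 7.1%.
- H = 12: sqrt(10/11) = 0.953. Normal: 1.869 on 10 df, 9.1%. t on 11 df: 2.201 x 0.953 = 2.099, 6.2%.
- H = 24: sqrt(22/23) = 0.978. Normal 6.8%; t on 23 df 5.5%.

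**Unequal schools (simulation).** Rates are normal / t on H-1 df. The middle column uses 1,324 pupils, 20% attrition, ICC 0.01-0.03 and a coefficient of variation (CV) of school size of 0-0.5. The right column uses a binary outcome with assumed prevalence 15%, CV 0.5 and ICC 0.01-0.05.

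| Schools | Size CV 0-0.5 | Binary outcome, CV 0.5 |
|---|---|---|
| 8 | 12-16% / 7-10% | 15-16% / 9-10% |
| 12 | 9-12% / 6-8% | 11-12% / 8% |
| 20 | not run | 8-9% / 6-7% |
| 24 | 6-8% / 5-6% | not run |
| 40 | not run | 6-7% / 5-6% |

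**Effect of the strata (two balanced strata, simulation).**

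- Adjusted for stratum, equal sizes: 8 schools 16% / 10%; 12 schools 11% / 8%; 20 schools 8% / 6.5%.
- Not adjusted, with educational level explaining 25-50% of between-school variance: for 12 equal schools (ICC 0.02-0.05), 2.4-6.2% with a normal reference. Allowing unequal sizes and ICC 0.01-0.05, the t reference gives 1.7-7.0% at 8 schools, 1.4-6.1% at 12 and 1.7-5.2% at 24.

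**Comparator.** A t-test on one summary per school, with no stratum effect, stayed at 4.6-5.2% for every H from 4 to 90 in the binary simulation. A stratum-adjusted school-level t-test also holds about 5%.

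**The case against.** The strongest reply is that the article does not plan the analysis whose error rates are shown. It clusters on classes, of which there are enough, so the figures describe a corrected plan. That is right, and it is why the point is conditional. It still matters, because the cluster level has to be corrected and the retained method then fails to fit the design.

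A reader might infer that the trial will declare effects too often, for every outcome and at every wave. The documents do not support this. Stratification should balance educational level, so the covariate rule would probably leave it out of the model. If it is prognostic, the excess then shrinks or reverses. That is not a planned safeguard: it depends on an unstated share of variance, and an interval that is too wide is also wrong.

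A reader might also take the normal-reference figures as the planned test. The article names no reference distribution. A t reference roughly halves the excess without removing it. Degrees of freedom may properly be left to a fuller plan, so their absence is not the fault. The fault is the method that is named.

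Finally, small is not a number. The excess is clear up to about 20 schools and minor by 40.

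**Conclusion.** The point holds in conditional form. The article fixes a large-sample variance for a design that it describes as having few randomised units. With school as cluster and no stratum effect, the type I error at nominal 5% is roughly 7-16% with 8 schools, 6-12% with 12 and 5-8% with 24, across the two reference distributions. It is higher with stratum adjustment, and can be at or below 5% when a prognostic educational level is omitted. The direction for this trial cannot be settled, because the school count, the ICC and the influence of educational level are not given. The mismatch itself can be settled from the text. The error from clustering on classes is a separate matter and is not counted in these figures.

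**What to change.** For arm comparisons, replace the linearised variance with one of two approaches:

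- A school-level analysis: adjust at pupil level first, reduce to one summary per school, adjust for the educational-level strata, and use t on schools minus strata minus 1 degrees of freedom (8 schools in two strata: 8 - 2 - 1 = 5).
- An individual-level model with school as cluster, stratum adjustment, a bias-corrected variance and small-sample degrees of freedom suited to the outcome type. Kenward-Roger fits the continuous scale scores only, not the dichotomous outcomes.

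Report the number of schools and the degrees of freedom with the comparisons. A within-stratum permutation test is optional, and useful only with enough schools. Eight schools in two strata of four give 6 x 6 = 36 allocations and a smallest two-sided p of 2/36 = 0.056; four strata of two give 16 and 2/16 = 0.125.

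The cost is analysis wording, with no new data. Intervals will be wider and nominal power somewhat lower.
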